**4. Abstract**

*Design:*

A pragmatic, randomised controlled trial and economic evaluation to investigate the effectiveness and cost-effectiveness of the self-directed E-Couch social anxiety module versus a waiting list control condition, for reducing sub-clinical social anxiety symptoms in the general population.

*Study Population:*

Respondents (aged 16+) to a direct-to-consumer advertisement placed on national websites who have social anxiety symptoms but do not meet the criteria for social anxiety disorder (this latter group will instead be advised to seek help).

*Intervention and Control:*

Intervention is the E-Couch social anxiety module, a self-guided intervention. Control group receive no intervention and are placed on a waiting list to receive the intervention at the end of the trial. Both groups receive email and text message reminders.

*Outcome Measures:*

Change in self-reported social anxiety score using the Social Phobia Inventory (SPIN). Secondary measures: Brief Fear of Negative Evaluation scale (8 item BFNE-S); SOPHS Social Phobia screener; depression (CES-D); mental wellbeing (SWEMWEBS); quality of life (SF36); use of mental health services; safety events; adherence, retention and attrition rates. All measures at 6 weeks, 3, 6 and 12 months.

*Analysis:*

A mixed effects model will be used to analyse the primary outcome (intention to treat analysis).

*Sample Size:*

2104 participants (1051 per group) will provide 90% power to detect a small between group effect size of Cohen's d=0.2 at 5% two-sided significant level, accounting for a high level of potential attrition of up to 50%.

*Economic Evaluation:*

A prospective economic evaluation, conducted from a NHS and social care perspective, to provide estimates of cost utility and cost-effectiveness.

*Embedded Qualitative Study:*

Interview study with 20 participants at the end of the study to explore issues including acceptability, adherence, retention, attrition. Also, during the study, in the case of high loss-to-follow-up we will also undertake interviews with a sample of up to 10 participants in the intervention arm, who did not complete their 6 week follow up, to understand some of the reasons behind this.

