**5. Lay Summary**

Social anxiety symptoms cause major problems for many people. The problems tend to last for years and people often do not seek help. Seeing a therapist for face-to-face cognitive behavioural therapy is recommended by NICE as the most effective approach for social anxiety disorder. We also know that many people have 'sub-clinical' social anxiety symptoms which cause them problems but are not severe enough to be diagnosed as 'social anxiety disorder'. We know many of these people turn to the internet to look for help where various unguided, self-directed internet-based tools are being made widely available - but there is very little evidence to say whether or not these are helpful.

We propose to test out the value of an internet self-help package (E-Couch) for sub-clinical social anxiety symptoms in the general population in a randomised controlled trial. We intend to provide E-Couch (or the ‘control’ website) to about 2000 people. These people will have social anxiety symptoms but not social anxiety disorder. For the people who are likely to have social anxiety disorder we will direct them to seek evidence-based help from the NHS, as recommended by NICE.

Over a period of 12 months we will measure the effect of using E-Couch self-help on social anxiety symptoms, as well as on quality of life, mental wellbeing, depression and general anxiety, and their use of other sources of help.

Harnessing the internet to help with a common problem among the general population has great potential to deliver low cost, widely accessible public mental health interventions. Our project will also give the opportunity to learn more about the value of using the internet to do this, and what the opportunities and challenges are - for researchers as well as for service providers and the public.

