**10. Study Design**

*Summary*

A large, pragmatic, double-blind, randomised controlled trial of the internet-based self-directed E-Couch social anxiety module versus a waiting list control condition, for the treatment of sub-clinical social anxiety symptoms, among a general population sample recruited using direct-to-consumer advertisements placed on national websites.

*Our intervention*

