
The E-Couch toolkit is available online for anyone who registers to use it (<https://ecouch.anu.edu.au>). For this study a social anxiety specific tool will be packaged using the e-couch social anxiety content to create the intervention. We do not anticipate high levels of contamination in the control arm – we will not call the intervention ‘e-couch’ in this study (it will be given a new, study-specific name), and e-couch (and the social anxiety elements within the toolkit) are not widely known or used by the UK population. We will measure contamination and use of any other online social anxiety tools through participant self-report at the time of final follow-up, using a bespoke questionnaire asking respondents which of a list of online interventions they have or have not also accessed during the study period. This is a pragmatic study and we would expect some participants to also be seeking other self-help, in both arms of the study.

*Control group*

The control group receive no intervention and are placed on a waiting list to receive the intervention at the end of the trial.

*Study population*

Internet users who consent to take part in a study for self-help with sub-clinical social anxiety symptoms. To be eligible they must have some level of social anxiety symptoms, defined as scoring 13 or more on the SPIN instrument (the population mean is generally 11 or 12, so the score of 13+ was chosen to pick up people with mild symptoms. People who score over 20 are more likely to have social anxiety disorder).

This is an amendment to the original protocol that required eligible participants to score 13-19 on the SPIN instrument. However it became clear after 6 months of recruitment that very few individuals score in this range, and most people with any level of social anxiety symptoms score more highly.

*Recruitment*

We will use advertisements placed on websites including NHS Choices, the NHS website, which receives more than 25 million unique visits per month making it one of the most visited websites in the UK and certainly the most popular health website. It is also a widely trusted source of health information and the NHS branding is known to facilitate recruitment to research studies [Todkill & [name], 2013]. As noted above, the current team used advertisements on the NHS Choices website very successfully in a previous trial of an e-therapy intervention, recruiting 3070 individuals in a 2-week period [[name] et al., 2013].

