*Eligibility screening and consent*

Individuals expressing an interest in the online advert by clicking on a web link will be directed to a University website containing full information on the trial and the opportunity to ask questions of the study team by email or telephone.

They will be invited to complete screening questions which will determine whether they are eligible for participation: they will need to confirm the following: a working email address (to respond to a confirmation email and receive reminders), a mobile phone number (to receive text reminders), and that they are aged 16 or over and resident in the UK. We will exclude people who are currently receiving therapist-guided treatment for social anxiety disorder. If they meet these criteria, they will be asked to provide online consent. In line with our public health approach and the pragmatic nature of this study, our inclusion criteria have been kept very broad. Having given informed consent, participants will know that they are free to withdraw at any time without giving a reason and without it affecting their care.

In providing consent, participants will give their agreement to complete two screening measures (the SOPHS and the SPIN) and to be randomized to one of two conditions (E-Couch intervention or waiting list control). The consent will also give their agreement to be contacted by email and text message to send them study reminders. Separate consent will be sought for any qualitative interview as part of the study. Participants will be eligible if they score 13 or more on the SPIN.

We do not want to delay any form of help-seeking and all participants with a score>19 on the SPIN will be given advice to seek therapist-guided help from the NHS (including IAPT) as their scores indicate they may have social anxiety disorder (note that we have excluded people currently receiving treatment).

In order to inform future research and to support some exploratory analyses of our data we will include the new SOPHS social phobia screener (<http://nimhr.anu.edu.au/mental-health-measures/social-phobia-screener-sophs>) at this screening stage, although it will not be used for screening at the time (only in post hoc analyses).

*Initial trial flow and collection of baseline measures*

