In addition to the SPIN and SOPHS, eligible participants will be required to complete a battery of self-report baseline questionnaires, and in line with all other trial procedures these will be collected online through the trial portal. These questionnaires will collect demographic characteristics (age, sex, education, employment, marital status etc.), and we will measure social anxiety symptoms (SPIN and SOPHS as above, and Brief Fear of Negative Evaluation BFNE-S scale), depression (CES-D), mental wellbeing (SWEMWBS), quality of life (SF-36), and current use of health services and psychological interventions (including self-help).

Once baseline measures are completed, eligible participants will be randomized in a 1:1 ratio with no stratification, using computer generated random number sequence run through an automatic online programme. Participants in the intervention arm will be given access to a password-protected website and will be encouraged to access and use the self-guided intervention over a period of up to 6 weeks (although they can work through the intervention at their own pace). They will receive one text message within 24 hours of randomisation to thank them for participating and to remind them to access the intervention, and one further text message towards the end of the 6 week period to thank them again and to remind them that they will shortly be asked to complete follow-up measures. They will also receive three email reminders during the six-week period (both intervention and control will receive the reminders – at 1 week, 3 weeks, and 5 weeks). Participants in the Control arm will receive the same reminders and will be given access to the intervention after final follow-up (12 months). Participants in the intervention arm will be offered continued access to the intervention once the trial is completed.

*Follow-up measures*

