Self-report follow-up measures of social anxiety symptoms (SPIN, SOPHS, and Brief Fear of Negative Evaluation BFNE-S scales), depression (CES-D), mental wellbeing (SWEMWBS), quality of life (SF-36), and current use of health services and psychological interventions, and time off from work or study due to psychological problems will be taken at 6 weeks (following completion of the self-guided intervention), 3 months, 6 months, and 12 months. At each follow-up point they will receive notification of follow-up measures by email and by text message, and if measures are not completed they will receive up to three follow-up emails.

We will also record usage data (total number of logins, total page views, time on site). We will record measures of adherence to the intervention (number of components of E-Couch completed) and attrition from the trial (loss-to-follow-up at each time point). We will also record any safety (adverse) events (captured through monitoring participant feedback, and through questions at each follow-up period). We do not anticipate adverse events in a trial of a low intensity online self-help tool for a subclinical population. However our adverse event monitoring will include assessment of feedback from participants (including routine questions asked at each follow-up period as well as ad hoc correspondence such as emails or telephone calls) to see if these report an issue such as distress or anxiety caused by the intervention. In the first instance any possible adverse event will be reviewed by the study team (trial manager in discussion with lead investigator), and immediate action taken (such as withdrawing a participant who reports distress). If the event is classified as an adverse event it will be referred to the Trial Steering Committee (with independent chair) who will also have the role of Data Monitoring Committee for their consideration.

*Primary outcome measure*

This will be the change in self-reported social anxiety score using the 17-item SPIN. This measure has been shown to have adequate internal consistency, test-retest reliability, construct validity and sensitivity to change following intervention [Letamendi et al., 2009].

*Secondary outcome measures*

These will include social anxiety measured using the FNE scale; depression (CES-D); mental wellbeing (SWEMWBS); quality of life (SF-36); and safety events.

*Statistical methods*

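### The protocol calls the trial double-blind, but participants know their allocation and rate the primary and secondary scales themselves

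*Protocol*

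**What the plan says.** The Summary at the head of protocol section 10 (Study Design) calls the study "A large, pragmatic, double-blind, randomised controlled trial of the internet-based self-directed E-Couch social anxiety module versus a waiting list control condition". The blinding label and the waiting list stand in the same sentence.

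The rest of section 10 gives the operative detail:

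- **Control group:** "The control group receive no intervention and are placed on a waiting list to receive the intervention at the end of the trial".
- **Eligibility screening and consent:** participants agree "to be randomized to one of two conditions (E-Couch intervention or waiting list control").
- **Initial trial flow:** "Participants in the intervention arm will be given access to a password-protected website", whereas "Participants in the Control arm will receive the same reminders and will be given access to the intervention after final follow-up (12 months").
- **Primary outcome measure:** "This will be the change in self-reported social anxiety score using the 17-item SPIN". The follow-up scales for social anxiety, depression, wellbeing and quality of life are also self-reported, and all trial questionnaires are collected online.

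The design statement in section 4 (Abstract) opens with "A pragmatic, randomised controlled trial and economic evaluation" and claims no blinding. Section 5 (Lay Summary) describes the control differently from every other section: "We intend to provide E-Couch (or the ‘control’ website) to about 2000 people".

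**The concern.** Double-blind is a statement about who does not know the allocation. In a trial whose primary outcome is a self-rated symptom scale, it tells the reader that the person scoring the scale did not know which arm they were in. If that is untrue, the reader is misinformed about a property that bears directly on the primary result.

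The target effect is small (d=0.2), so a modest difference in how the two arms report symptoms would be a material part of it. The protocol also commits to CONSORT reporting and to publishing the final protocol (sections 10 and 12), so the label could pass into public accounts of the trial.

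**Working it through.** **1. Can the participant be blind?** Setting the parts of section 10 side by side:

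| Question | What the protocol provides | Consequence |
|---|---|---|
| What is disclosed at consent? | Both conditions, including the waiting list | Each participant knows what the two arms are |
| What does the intervention arm receive? | Website access after randomisation | Allocation is evident |
| What do controls receive? | The same reminders, and access only after 12 months | Allocation is evident |
| Is there a sham or placebo site in section 10? | No | Nothing conceals the difference |

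The identical emails and texts balance contact between arms but do not hide who has the website. The study-specific name for the intervention is given as a way to limit contamination. It does not mask allocation either.

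**2. Is there a blinded assessor?** The SPIN, SOPHS, BFNE-S, CES-D, SWEMWBS, SF-36 and service-use questions are all answered by the participant, so the assessor is the unblinded person. Site usage, adherence and attrition are recorded separately, but they are not the clinical outcomes on which the treatment effect is judged.

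**3. Is any other role masked?** The protocol describes no masking of investigators, trial staff or analyst. Analyst masking could be set out in the SAP, which is not to hand, but it would not make participants or outcome assessment blind.

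**4. Does the lay summary supply a placebo?** It mentions a control website. The Abstract and the Control group and Initial trial flow parts of section 10 give controls no intervention and a wait. The lay summary is the only place where such a site appears.

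**5. Does any stated figure depend on the label?** Inputs from section 10, Sample size: d=0.2, 90% power, two-sided 5%, attrition up to 50%. Allocation is 1:1.

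- Evaluable per arm: n = 2(1.960 + 1.282)² / 0.2² ≈ 525.4, rounded up to 526.
- After attrition: 526 / (1 − 0.5) = 1052 per arm, or 2104 in total.

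This reproduces the planned number, and blinding does not enter the formula.

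**6. Why the label matters at this effect size (illustration only).** The documents give no size for reporting bias, so the values below are assumptions. With 526 evaluable per arm, the standard error of the difference in SD units is √(2/526) = 0.0617. If the true effect were zero and reporting differed by b, the chance of p<0.05 is 1 − Φ(1.96 − b/0.0617) + Φ(−1.96 − b/0.0617):

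| Assumed b (SD) | Share of d=0.2 | Chance of p<0.05 |
|---|---|---|
| 0 | 0% | 5% |
| 0.05 | 0.05/0.2 = 25% | 13% |
| 0.10 | 0.10/0.2 = 50% | 37% |

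The table shows sensitivity. It does not estimate bias in this trial.

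**The case against.** The strongest reply is that this is one unsupported adjective in one summary sentence. That sentence also names the waiting list, the abstract omits the word, and the self-report nature of the measures is stated openly. A careful reader can see that participants know their arm. Any reporting bias comes from the waiting-list design and would exist under either label, and no number changes. All of this is fair, and it limits the point to a wrong statement of a design property. It does not make the statement right.

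Several stronger readings are tempting, and the documents do not support them:

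- **That the protocol claims protection from expectancy bias.** It never says so in words. That is only what the label implies.
- **That the result will be inflated by a known amount.** The bias sizes above are assumed, and the net direction of all influences is unknown. Section 10 (Statistical methods) itself notes that controls seeking other help could shrink the observed effect, and it plans mediation analyses of that.
- **That adverse-event review needs the allocation.** The Follow-up measures text describes examining what participants report. It does not say that the allocation is used.
- **That the analyst is unmasked or the registry entry is wrong.** The SAP and the registry record are not available, so neither can be asserted.
- **That a placebo site was planned.** The lay summary's phrase, with its own quotation marks around the word control, is too thin to show that.
- **That the waiting list is the wrong comparator.** It may be a justified pragmatic choice. The error is the label.

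**Conclusion.** The point holds as a contradiction within the protocol. The study design summary asserts double-blinding. The consent, control, trial-flow and outcome text shows that participants know their allocation and are the assessors of the primary and secondary scales. The protocol describes no masked role.

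The conclusion rests only on the protocol's text and needs no outside source or assumed figure. The sample size of 2104 and the 90% power stand unchanged. The consequence is for interpretation: a difference near d=0.2 on the SPIN would compare E-Couch with knowingly waiting, and expectancy or response bias of unknown size would not be excluded. The label should be corrected because it misstates a core design property that bears on the primary result, and the correction costs almost nothing.

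**What to change.** 1. In section 10, Summary, remove double-blind. State that participants, who report the outcomes themselves, are not blinded. If any role is in fact masked, name it.
2. In the CONSORT report, describe the trial as unblinded for participants and for outcome assessment.
3. Interpret the primary result as E-Couch against a known waiting list, and say that expectancy or response bias of unknown size is not excluded.
4. Reword the lay summary sentence so that it agrees with the no-intervention waiting list, for example by saying that about 2000 people will be randomised either to use E-Couch straight away or to wait and receive it at the end. Deleting the bracketed phrase alone would leave the sentence saying that everyone is given E-Couch during the trial.

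The cost is wording only. No sample size, model, outcome or schedule changes. The one downside is a less favourable design label.

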**11. Ethics and Governance**

We will obtain all ethics and governance permissions prior to project start and have significant experience in doing so previously. The trial protocol will be registered with ISRCTN. One of the key ethical issues for us will be to ensure we comply with the NICE guideline on social anxiety disorder, and as stated above if individuals likely to have social anxiety disorder (SPIN=19+) are identified then we will make sure they have clear advice to seek help from existing services for the NICE-recommended treatments. .We will collect data on their use of health services throughout the trial period.

We will require University ethics committee approvals from the University of Oxford and the Australian National University. We have received confirmation that we do not require NHS ethics approval (confirmed with the Health Research Agency (HRA)).

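### The SPIN cut-off for advice to seek help is above 19 in the eligibility text but 19 and above in the ethics section, so a score of exactly 19 falls under two opposite rules

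*Protocol*

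**What the plan says.** Three places in the current protocol text put a SPIN boundary on possible or likely social anxiety disorder.

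- **Section 10, Eligibility screening and consent.** This is the operating rule: "all participants with a score>19 on the SPIN will be given advice to seek therapist-guided help from the NHS". The reason follows at once: "as their scores indicate they may have social anxiety disorder".
- **Section 11, Ethics and Governance.** This is the commitment made under compliance with the NICE guideline: "if individuals likely to have social anxiety disorder (SPIN=19+) are identified then we will make sure they have clear advice to seek help". The sentence refers back to what has already been said, so it is offered as a repetition of the operating rule and not as a new one.
- **Section 10, Study population.** A bracketed remark explaining the choice of 13 as the entry score says: "People who score over 20 are more likely to have social anxiety disorder". No advice or other action is attached to it.

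Entry to the trial is governed by a separate threshold: "Participants will be eligible if they score 13 or more on the SPIN". There is no upper limit. The same section notes that this replaced the "original protocol that required eligible participants to score 13-19 on the SPIN instrument".

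**The concern.** The advice is the means by which the protocol avoids delaying help for people who may have the disorder. Section 11 names compliance with the NICE guideline as a key ethical issue and relies on this advice to achieve it. It carries more weight now that the upper entry limit has gone: people with higher scores are randomised 1:1, and the control arm waits until after the 12-month follow-up for the intervention. A trigger for such advice should have one value. Here the operating rule and the ethics commitment disagree, so whichever is applied departs from one of the two sections.

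At stake is whether participants at one particular score receive advice that the ethics section promises. No estimate of the treatment effect depends on it.

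**Working it through.** No sample size, power or error-rate figure is involved, and the plan gives no number to reproduce. The check applies each stated boundary to the scores around it.

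Inputs:
- Operating rule (section 10, Eligibility screening and consent): advice if SPIN > 19.
- Ethics rule (section 11): advice if SPIN ≥ 19, reading 19+ as 19 and above.
- Descriptive remark (section 10, Study population): more likely disorder if SPIN > 20, with no action.
- Assumption: SPIN totals are whole numbers. Then > 19 starts at 20, ≥ 19 starts at 19, and > 20 starts at 21.

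| SPIN score | Advice under the eligibility text | Advice under the ethics section | Within the over-20 description | Result |
|---|---|---|---|---|
| 18 | No | No | No | All agree |
| 19 | No | **Yes** | No | Advice rules conflict |
| 20 | Yes | Yes | No | Same action, different label |
| 21 and above | Yes | Yes | Yes | All agree |

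Reading the table:
1. The two rules that carry an action differ at one value only, 19.
2. The labels differ at two values. A score of 19 counts as likely disorder in the ethics section and falls outside the other two boundaries. A score of 20 is covered by the eligibility text and the ethics section but lies outside the over-20 remark.
3. All the scores in the table are at or above 13, so every one of these people is eligible under every reading. The conflict cannot change who is randomised.
4. The superseded entry range of 13 to 19 has scores above 19 as its upper complement, which matches the eligibility text. It does not settle the conflict, because it was an entry criterion, it is no longer in force, and section 11 still states 19+.

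**The case against.** The strongest reply is that this is a one-point slip in wording that touches almost nobody. Section 10 reports that after six months of recruitment very few individuals scored from 13 to 19, and those at exactly 19 are only part of that group. The conflict does not reach eligibility, allocation, sample size or the primary analysis, and nothing in the protocol stops someone scoring 19 from seeking help. All of this stands, and it sets the severity. It does not remove the contradiction: both statements are current text, both attach the same advice, and one claims to repeat the other.

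Three stronger readings are tempting, and the document does not support them.

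- **Three cut-offs for one decision, with scores of both 19 and 20 handled differently.** Only two of the three places trigger anything, and both give advice at 20. The over-20 remark says such people are more likely to have the disorder. It does not say that only they are.
- **The trial website applies the rule automatically, so one section must already have been broken in the programming.** The protocol says that questionnaires are completed online and that randomisation is automated. It does not say how the advice is triggered or delivered. Which rule was used has to be checked and cannot be assumed.
- **The baseline-severity subgroup has no single definition.** The statistical methods list baseline symptom level as a moderator tested by interaction, with no cut-off. It could be analysed as a continuous score, and any cut-point may properly be left to the SAP. Randomisation is unstratified, so no stratum depends on these values either.

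**Conclusion.** The contradiction is real and narrow. The advice rules in sections 10 and 11 conflict at a SPIN score of exactly 19. The descriptive boundary in the study population text adds inconsistent labelling at 19 and 20 but no difference in handling at 20.

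The severity is minor. The number affected cannot be computed, because the protocol gives no distribution of scores. It is likely to be small if the pattern reported from the first six months of recruitment continued. There is no effect on eligibility, randomisation, sample size or the primary analysis. The point still deserves correction because it concerns a protection promised to participants.

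The conclusion rests on whole-number SPIN totals and on reading 19+ as including 19. It takes no position on which cut-off is clinically right.

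**What to change.** Reconcile section 10 (Eligibility screening and consent) and section 11 to a single cut-off, written in one unambiguous form in both places, and align the descriptive remark in section 10 (Study population) with it. The clinical investigators should choose the value, and it should be consistent with what the ethics committees approved.

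Then establish which rule was applied in practice. If it was the above-19 rule, list the participants who scored 19 and did not receive the advice promised in section 11, and refer that list to the investigators and the oversight committee for a decision.

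The cost is a short wording amendment in up to three places, one check of the implemented rule, and a simple listing by screening score. No reanalysis and no change to recruitment are needed.
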